### Randomization, concealment of allocation, and blinding

A subgroup of treating healthcare providers (physicians and nurses) will solicit interest in the study during their clinic appointments and based on clinic lists of their eligible patients compiled by research staff. The program is not being trialed with all IBD clinicians at all sites; this is appropriate for a Hybrid 1 design. Willing participants will then be consented by research staff who will also randomize them at enrollment (1:1) by research staff using two strata: center of care and IBD-DI severity (no/mild disability (scores of 0–34) vs. moderate/severe disability (scores of 35–100)) to ensure balance between the intervention and control arms in those strata. Randomization will occur directly in the REDCap (Vanderbilt University, Nashville, TN) database using the randomization function [23] and allocation will be concealed. Blinding is not possible as the transition navigators need to interact directly with the participants and their treating healthcare teams.

### Interventions

Intervention Group: Participants assigned to the intervention group will receive a multimodal intervention consisting of four core components.

#### Core component 1: individualized assessment

Each enrolled patient will undergo an individualized assessment of their biopsychosocial risk profile (Pediatric IBD INTERMED [24]), self-efficacy (IBD-SES-A) [25], functioning (IBD-DI) [26, 27], transition readiness (TRAQ) [28] and IBD knowledge (IBD-KID2) [29], administered by the transition navigator (see below) or research staff. In addition, supplemental questionnaires will be administered to assess depression, anxiety, and activation (i.e., a participant’s level of engagement in their own care); these will be self-administered by the participant with subsequent review by the transition navigator (Table 1).

**Table 1 Tab1:** Tools used for individualized assessment and corresponding domains

Core skills	Questionnaire	Domains
*Main questionnaires*		
Coping/self-regulation*	IBD Disability Index (IBD-DI)	Functions, Activity participation, Structures, Environmental factors
Comprehensive	Pediatric IBD INTERMED	Biological, Psychological, Social, family/caregiver, Health systems
Assertiveness/self-efficacy	IBD Self-efficacy Scale for Adolescent (IBD-SES-A)	Self-confidence, Health-related quality of life
Tasks/knowledge	Transition Readiness Assessment Questionnaire (TRAQ)	Self-management, Self-advocacy
	Inflammatory Bowel Disease Knowledge Inventory Device Version 2 (IBD KID2)	Knowledge
*Supplementary questionnaires*		
Depression	Patient Health Questionnaire-9 (PHQ9)	
Anxiety	Generalized Anxiety Disorder-7 (GAD7)	

The INTERMED, PHQ9, and GAD 7 may be repeated as needed by the navigator to establish progress and update participants’ risk profile

The Pediatric IBD INTERMED is a validated instrument that assesses five domains of health (biological, psychological, social, family/caregiver and health system) reflecting historical/developmental, current state and future prognosis/vulnerability [24]. The instrument is is designed to facilitate inter-professional clinical communication and should identify issues related to the different domains of health. Identified psychosocial needs will be addressed by the care team, and/or in the skill-building component. The Pediatric IBD INTERMED and supplemental questionnaires may be repeated as determined by the navigator to establish progress and update the patient’s psycho-social risk profile.

All questionnaires will be administered at study enrollment, the time of transfer to adult care, and intervention completion.

#### Core component 2: transition facilitation with a navigator

Participants will be assigned one of two project-based transition navigators. The navigator roles will be staffed by a healthcare provider (nurse, nurse practitioner, or social worker) with knowledge of IBD, an understanding of the care pathway involved in transitioning IBD patients, and the skills and ability to provide psychosocial support.

The transition navigators will:Administer the individualized assessments (core component 1) and identify AYA needs and gaps in knowledge.Identify ‘red flags’ (e.g., suicidality, severe active symptoms/signs of IBD) requiring immediate physical or mental health intervention using the results of the Pediatric IBD INTERMED and the HEEADSSS psychosocial interviewer technique [30–32] and refer these issues to the patients’ healthcare team or other relevant professionals for potential management.Engage in personalized skills-building exercises with the AYA, and/or refer them on to skills-building virtual activities (*core component 3*).Establish goals of transition with the AYAs and their family/caregiver-guardians (*core component 3*).Facilitate access and completion of the eLearning curriculum (*core component 4*).Act as a central point of contact to answer the AYA’s questions, address concerns, ensure the AYA adheres to appointments and medications, and helps the AYA navigate the health system effectively.

The navigators will work remotely with the AYAs and their families, engaging via the AYA’s preferred technology: video teleconferencing, instant messenger (IM), telephone. The frequency of contact with the navigator will be driven by the participant, with a minimum number of contacts determined as twice yearly for most of the follow-up period, and two additional meetings in the year around transfer (6 months before and after the transfer date). At each visit, the navigator will complete a standardized Case Reporting Form (CRF) using REDCap to document discussions, assessments conducted, and a clear plan for intervention and/or discussion at the next exchange.

The interventions administered by the transition navigators and timeline are described in Table 2.

**Table 2 Tab2:** Timeline and structure of the intervention provided by the transition navigator (*core component 2*)

Study time period	Activities of the transition navigator
Enrollment phase: T_o_ → 2 months after randomization	Pre-meeting with CD care team: This will consist of a case-review between the navigator and HCPs to review the AYA’s medical and psychosocial history, describe the plan for transition and establish a coordinated care pathway to be facilitated by the navigator. Among AYAs with an uncomplicated history, this review and planning could be done by email; otherwise, video teleconference software will be used Introductory meeting with the AYA and guardians/caregivers: The navigator will summarize the care pathway, the individualized goals of the intervention and answer basic questions about transfer to adult care. The navigator will establish SMART (Specific, Measurable, Achievable, Realistic, Time-based) goals for the family and AYA Second meeting with AYA alone: This meeting is intended to build trust, establish the limits of confidentiality, methods of communication, and boundaries. The navigator will propose SMART goals which may be distinct from the goals established with the family Meeting for individualized assessment: The aforementioned assessment tools will be administered (Core Component 1). Note: At the AYA’s discretion, this meeting may be combined with the meeting with the AYA alone and/or the meeting with guardians/caregivers
Maintenance phase: 2 months after randomization→ 1–2 years after transfer	The frequency of the virtual meetings during the maintenance phase will be flexible, with a minimum of 2 visits per year, depending on the needs and willingness of the AYA In the year around transfer (from 6 months prior to transfer, to 6 months after transfer), a minimum of 3–4 meetings will be planned A detailed script will be provided to the navigators to ensure a standardized list of topics are covered. The navigator will also work with the AYA and healthcare team to address deficits based on the AYA’s answers. Example questions to be asked by the navigator include: How are you finding the quality of your health care? How are things going with the biologic infusion clinics and the Patients Services Program (if applicable) How are you filling your prescriptions? How are the cost of your prescriptions covered? Do you know how to work with your insurance company to ensure your medications are covered? How did your visit with the doctor go? Did you parents go with you? How was your visit with the adult doctor? Did you find her/him approachable and knowledgeable? Did you feel you had enough time with the doctor? Did the adult doctor talk to you about colonoscopy, and how that might differ from colonoscopy in a pediatric hospital? What are you plans for post-secondary school work/university/college? Have you investigated your university’s disability program, and any accommodations to which you might be entitled because of your IBD?
Conclusion phase: end of study	Ongoing feedback of clinical and psychosocial concerns with adult GI Intervention completion will depend on patient readiness and the success of the skill-building exercises (*Core Component 3*), typically 1–2 years after transfer depending on age at enrollment Final assessments will be administered by the navigator at the final visit (*Core Component 2*), and the AYA will be instructed on how to complete the outcome measures

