#### Core component 4: structured educational eLearning curriculum

The aim of the education component is to provide consistent, accessible, and interactive information on key topics across 4 themes: healthy lifestyle, transitioning to adult care, self-care, and practical approaches to IBD-related tasks. The content is in development by the CIDsCaNN Education Committee and will be refined by experts, including adolescent medicine specialists, adult gastroenterologists, nurses, social workers, and other patients with IBD. eLearning modules will be created for each topic and AYAs living with IBD will advise regarding suitable formats for content delivery. A comprehensive manuscript detailing eLearning curriculum development is planned for future submission.

The navigator will provide participants with access to the curriculum, along with expectations for completion. Successful curriculum completion will be defined as completion of ≥ 80% of the mandatory modules. The eLearning modules will be piloted by the Patient Advisory Board (see below) and continuously improved based on feedback received from AYAs, the healthcare providers, and the navigators.

Control Group: The control group will receive the routine care transition supports currently available at each participating Canadian pediatric center. While every Canadian IBD center intervenes differently in transitioning AYAs, most have a semi-structured transition program. In order to standardize the control intervention, all participating centers will implement the following transition process:A written letter explaining the goals of transition to the participants and their family.Completion of age-appropriate checklists to ensure adolescents are meeting milestones of transition (developed by the TRACC Network) [35].Online live educational webinars on transition and adolescent issues (once yearly, hosted by the CIDsCaNN Education Committee).Individualized assessment (core component 1) at enrollment, the time of transfer, and study termination. Results of the Pediatric IBD INTERMED will be shared with the clinical team to provide intervention where indicated.Completion of a transfer-of-care summary letter sent to the receiving adult gastroenterologist using a standardized letter template [36].

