While the control group may also receive other transition supports currently in place in their participating care center, they will not receive the formal 4-component intervention described above. Their interaction with the navigators will be limited to completion of the INTERMED and other secondary outcomes measures.

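### The protocol lets the intervention arm's own navigator collect the primary outcome (IBD-DI) and leaves open who collects it in controls, so the assessor can differ by arm and no masked or common assessor is provided

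*Protocol article*

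**What the plan says.** The primary outcome is the IBD-DI at the end of the treatment period (Statistical analysis). Core component 1 lists the IBD-DI among the main questionnaires, which are "administered by the transition navigator (see below) or research staff". For the supplemental depression, anxiety and activation questionnaires it says instead that "these will be self-administered by the participant with subsequent review by the transition navigator". The same section schedules all questionnaires at enrolment, at transfer and at intervention completion.

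For the intervention arm, the conclusion phase in Table 2 (Core component 2) says "Final assessments will be administered by the navigator at the final visit". The sentence goes on to say that "the AYA will be instructed on how to complete the outcome measures". On staffing, Core component 2 says "Participants will be assigned one of two project-based transition navigators". These navigators also set goals, provide support and, under Core component 3, act as motivational coaches.

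For the control arm, the control-group paragraphs at the end of the Core component 4 section include "Individualized assessment (core component 1) at enrollment, the time of transfer, and study termination". They then restrict contact: "Their interaction with the navigators will be limited to completion of the INTERMED and other secondary outcomes measures".

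On masking, the randomization section says "Blinding is not possible as the transition navigators need to interact directly with the participants and their treating healthcare teams". The article describes no masked outcome assessor.

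**The concern.** The IBD-DI asks participants about their own functioning, so the answers can depend on who asks and on the relationship between the two. If a participant's coach collects the score in one arm and a relative stranger collects it in the other, any effect of the assessor is confounded with treatment. No analysis of the trial data can then separate the two.

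The reason given for not blinding concerns delivery of the program. It does not explain why those who deliver the program should also collect the final score. Under Limitations, the protocol considers only a monitoring effect that improves control results and so works against a false positive. It does not consider an assessor effect in the other direction.

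**Working it through.** **Who collects the final IBD-DI, from the text**

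| Question | Intervention arm | Control arm |
|---|---|---|
| Is the IBD-DI due at study end? | Yes (Core component 1; Table 5) | Yes (core component 1 is repeated at study termination) |
| Who may give it under Core component 1? | Navigator or research staff | Navigator or research staff |
| What does the arm-specific text say? | Navigator gives the final assessments (Table 2) | Navigator contact covers the INTERMED and other secondary measures only |
| Has that navigator coached the participant? | Yes | No |
| Is a masked assessor described? | No | No |

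There are three possible readings.

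1. *The control-group restriction is taken literally.* The IBD-DI is the primary measure, so navigators do not give it to controls and research staff must. The type of assessor then differs by arm.
2. *The restriction is loosely worded.* Core components 1 and 2, with the control-group list, would let navigators give controls the IBD-DI. The type of assessor is then the same, but it is an unmasked person who has coached one arm only. The restriction also conflicts with the other passages.
3. *The outcome measures are self-completed after instruction.* The second half of the Table 2 sentence permits this. The instruction still falls within the concluding navigator phase in the intervention arm, and no equivalent is described for controls.

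No reading gives a collection procedure that is stated to be the same in both arms and independent of program delivery.

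**What an arm-dependent shift would do (illustration)**

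The protocol gives no figure for assessor bias, so there is none to reproduce. The inputs taken from its sample-size text are:

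- SD 20.5 and planned difference 16 points. The standardized effect is 16/20.5 = 0.78, which matches the protocol.
- 45 enrolled per arm with 25% drop-out. Completers are 45 × 0.75 = 33.75, about 34 per arm.
- Wilcoxon-Mann-Whitney test at P < 0.05. The protocol does not state sidedness, and two-sided is assumed here.

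The assumed shifts are 2 and 3 points:

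- 2/20.5 = 0.098 SD, and 2/16 = 12.5% of the planned difference.
- 3/20.5 = 0.146 SD, and 3/16 = 18.75% of the planned difference.

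A simulation with normal scores, SD 20.5, no true effect, 34 per arm and 20,000 runs per setting gave:

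| Assumed shift (points) | Rejected, two-sided | Rejected in favour of intervention |
|---|---|---|
| 0 | 4.9% | 2.4% |
| 2 | 6.7% | 5.7% |
| 3 | 8.6% | 8.0% |

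A closed-form check uses the Wilcoxon efficiency of 0.955 for normal data. The non-centrality is (shift/SD) × √(0.955 × 34/2) = (shift/SD) × 4.03.

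- 2 points: 0.0976 × 4.03 = 0.393. Rejection rate = Φ(−1.960 + 0.393) + Φ(−1.960 − 0.393) = 0.059 + 0.009 = 6.8%.
- 3 points: 0.1463 × 4.03 = 0.590. Rejection rate = Φ(−1.960 + 0.590) + Φ(−1.960 − 0.590) = 0.085 + 0.005 = 9.1%.

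The two methods agree on about 7% and about 9%.

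**The case against.** A reader might infer that the protocol prescribes a different type of assessor in each arm. It does not go that far. Core component 1 allows navigators or research staff, Core component 2 makes giving these assessments a navigator task, and controls receive the same assessment. The exclusion of the IBD-DI from control contact rests on the reference to other secondary measures, which may be loose drafting. The Table 2 sentence can also be read as separating navigator-led assessments from outcome measures that participants complete themselves. Both points stand, so arm-dependent collection is something the text permits and does not fix.

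A reader might also infer that the bias must favour the intervention and has a known size. Neither is supported. The shift used above is assumed, and any non-zero shift would raise the error rate. A trusted navigator could equally draw fuller disclosure and higher disability scores, which would work against the intervention.

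It can be said, too, that a condensed article leaves collection procedures to the full protocol. That holds for operational detail. Here, however, the article does state who administers what, and its statements do not fit together.

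Finally, a masked assessor would not cure reporting bias, because participants know their arm. That is true and limits what the fix can achieve, but it does not justify adding an avoidable difference between arms.

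**Conclusion.** The point holds in this form: the protocol allows the subjective primary outcome to be collected by a different type of person in each arm. On the alternative reading, an unmasked person who coached only one arm collects it in both. The stated reason for not blinding covers program delivery and not outcome collection.

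The size and direction of any bias cannot be estimated from the documents. A shift favouring the intervention is plausible. Under the assumptions shown (2 to 3 points, SD 20.5, about 34 completers per arm, normal scores, two-sided test), the false-positive rate would be about 7–9% in place of 5%. The conclusion does not depend on that illustration. It rests on the passages compared above and on the fact that an assessor effect confounded with arm cannot be removed in the analysis.

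**What to change.** - Reconcile Core component 1, the navigator task list and Table 2 in Core component 2, and the control-group paragraphs, so that one mode and one type of assessor are stated for the IBD-DI in both arms at every time point, above all at study end.
- Use one of two routes, both within resources already named: self-completion through a REDCap link, or administration by research staff who take no part in program delivery and, where feasible, are not told the arm. Research staff also randomize, so the person who randomized a participant should not be that participant's assessor.
- State that navigators neither administer nor instruct on the final IBD-DI. A wider ban on navigators seeing final questionnaires is not needed. It would remove their planned review of the depression and anxiety scales, which should stay as written, as should their review of the other questionnaires.
- Limit the statement that blinding is not possible to participants and those delivering care.

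The cost is small: one questionnaire moves to existing staff or to the existing database. According to Data Availability, recruitment had not begun when the article was submitted. The downsides are some unmasking of assessors, possibly slightly lower completion than at a navigator-led visit, and participant reporting bias that no assessor arrangement removes.

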Deficits in emotional self-management domains	Motivation and troubleshooting of barriers between visits provided by the transition navigator. Assignment to elective modules as appropriate

The transition skills-building program will prioritize high-needs individuals, as determined in *core component 1*. After baseline assessment, the skills-building curriculum will be tailored to the youth’s needs and developmental level as assessed by the Pediatric IBD INTERMED, TRAQ and IBD-SES-A. Skills-building materials will be delivered via online pre-recorded videos that first teach skills with an experiential component. There will be a basic training package of modules to be completed within 3 months of enrollment. The navigators will support any necessary needs and training and provide further individualization beyond the videos. The second year will focus upon completion of behavioral therapy sessions and progression to disease-specific task interventions with the navigator. Year three of the intervention will focus on the active reassessment of skills and targeted repetition of skill building activities as necessary. See Table 3 for interventions specific to various skills deficits.

#### Core component 4: structured educational eLearning curriculum

The aim of the education component is to provide consistent, accessible, and interactive information on key topics across 4 themes: healthy lifestyle, transitioning to adult care, self-care, and practical approaches to IBD-related tasks. The content is in development by the CIDsCaNN Education Committee and will be refined by experts, including adolescent medicine specialists, adult gastroenterologists, nurses, social workers, and other patients with IBD. eLearning modules will be created for each topic and AYAs living with IBD will advise regarding suitable formats for content delivery. A comprehensive manuscript detailing eLearning curriculum development is planned for future submission.

The navigator will provide participants with access to the curriculum, along with expectations for completion. Successful curriculum completion will be defined as completion of ≥ 80% of the mandatory modules. The eLearning modules will be piloted by the Patient Advisory Board (see below) and continuously improved based on feedback received from AYAs, the healthcare providers, and the navigators.

Control Group: The control group will receive the routine care transition supports currently available at each participating Canadian pediatric center. While every Canadian IBD center intervenes differently in transitioning AYAs, most have a semi-structured transition program. In order to standardize the control intervention, all participating centers will implement the following transition process:A written letter explaining the goals of transition to the participants and their family.Completion of age-appropriate checklists to ensure adolescents are meeting milestones of transition (developed by the TRACC Network) [35].Online live educational webinars on transition and adolescent issues (once yearly, hosted by the CIDsCaNN Education Committee).Individualized assessment (core component 1) at enrollment, the time of transfer, and study termination. Results of the Pediatric IBD INTERMED will be shared with the clinical team to provide intervention where indicated.Completion of a transfer-of-care summary letter sent to the receiving adult gastroenterologist using a standardized letter template [36].

While the control group may also receive other transition supports currently in place in their participating care center, they will not receive the formal 4-component intervention described above. Their interaction with the navigators will be limited to completion of the INTERMED and other secondary outcomes measures.

